**Statistical Analysis**

All data will be analyzed by SPSS version 20 statistical package. The levels of significance will be considered at P lower than 0.05. Intention to Treat (ITT) will be applied for all primary and secondary outcomes data. Quantitative data will be reported as mean (SD) or (SEM), qualitative data will be reported as frequency (percent). Baseline data will be analyzed by ANOVA, Fisher’s exact test or X^2^ test. Linear regression models will be used to analyze the interaction effect and the main effects.

**Safety**

Any unfavorable reported symptoms will be recorded in specific forms and 4 weeks after cessation of intervention, all the remained will be asked about the compliance of intervention, personal attitude on this study and any adverse events will be reported even in follow up period.

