**Methods/ design**

This study is a factorial randomized controlled trial with 120 eligible patients with IBS that randomly assigned to 4 groups to take soy isoflavones, cholecalciferol or both or none of them in each group for 6 weeks. The follow up session will be at week 10. The primary outcome is symptoms severity and the secondary outcomes are quality of life, total score of disorder, levels of inflammatory markers in serum and blood cells, and the activity of fecal serine protease. The adverse events will be recorded during all sessions of this trial. This study has been approved by Ethics committee in National Nutrition and food Technology Research Institute (NNFTRI) and Digestive Diseases Research Institute (DDRI) in Tehran University of Medical Sciences (TUMS). The ethics committee code is 050459. The findings of this study will contribute to achieve novel effective and safe treatments.

**Discussion:** Up to our knowledge, it will be the first factorial RCT of the impact of soy isoflavones and vitamin D on symptoms severity, QOL, total score, inflammatory markers and fecal serine protease activity in IBS.

**Trial registration:** NCT02026518, clinical trials.gov

**Key words:** Irritable bowel syndrome, Nutrition, Vitamin D, Soy isoflavones, randomized clinical trial

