**Design**

This study is a double blinded RCT with factorial design. The study will be conducted in endoscopy clinic, Shariati Hospital, Tehran, Iran. This protocol has been approved by Ethics committee in National Nutrition and food Technology Research Institute (NNFTRI) and Digestive Diseases Research Institute (DDRI) in Tehran University of Medical Sciences (TUMS), Tehran, Iran. Written informed consent will be got from all participants after oral and written explanation about the procedure of the study.

The participants that enter to this study will be selected according to eligibility criteria and will be randomized by computerized block randomization method with block size of 6 and will take the intervention for 6 weeks. The participants will be followed up at week 10 (Fig. 1). The assigned four groups will be placebo of vitamin D and placebo of soy isoflavones (P+P), placebo of vitamin D and soy isoflavones (P+S), vitamin D and placebo of soy isoflavones (D+P), vitamin D and soy isoflavones (D+S). The capsule of soy isoflavones contains 10 mg of diadzein, 8.5 mg of genstein and 1.5 mg of glycetin that will be taken twice per day. The vitamin D pearl consists of 50000 IU cholecalciferol that will be taken one per 15 days.

The control group will be obtained by use of placebo of soy isoflavones or cholecalciferol instead of original pill. The placebo of each treatment is in the same color and size.

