**Exclusion criteria**

Use of soy isoflavones or vitamin D one year before the study; use of soy milk or soy nuts during study; diet changes during study; use of artificial sweetener 2 days before study; no desire to complete the study; adverse effect of supplement; pregnancy during study

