**Secondary outcomes**

QOL in IBS will be assessed by validated IBS- QOL questionnaire at week 0 and week 6. IBS- QOL questionnaire has 34 items on dysphoria (8 items), body image (4 items), health-oriented worries (3 items), sexual related worries (2 items), social behavior (4 items), intervene with every-day activity (7 items) and personal relationship (3 items) ([18](#_ENREF_18)). Total score of IBS, another secondary outcome will be determined by a VAS between 0 and 100 –mm to evaluate the effect of interventions on total severity of IBS at week 0, week 6 and week 10 (follow up)([17](#_ENREF_17)).

Fecal serine protease enzyme activity is the marker for gut hyperpermeability, as one of the secondary outcomes will be measured by enzyme- linked immunosorbant assay (ELISA) kit after collection of fecal samples, keep them in -80◦ C freezer and preparation by 5 ml Tris buffer and centrifuged in 3000 RCF for 10 min.

Ten ml fasting venous blood samples will be taken from all participants that separated in 3 microtubes: 1- a microtube with EDTA as anti-coagulant will be centrifuged at 3000 RCF for 10 min to separate plasma and whole blood. 2- a microtube without any type of anti-coagulants will be kept for 30 min at room temperature, then will be centrifuged at 3000 RCF for 10 min to separate serum. 3- a microtube with heparin as anti-coagulant will be used to separate PBMC and culture them followed by centrifuging at 2000 RCF for 15 min. Isolated PBMC will be used to compare the amount of Nuclear Factor κβ (NF- κβ) before and after the intervention. All separated samples will be collected quickly in crayotubes and will be transferred to -80◦ C freezer until experiments start. Sera will be recovered to determine the level of serum 25- OH vitamin D and Tumor Necrosis factor- α (TNF- α) at week 0 and week 6.

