**Statistical Methods**

**Sample Size**

According the factorial design, we consider required sample size to compare soy isoflavones group versus control group and vitamin D group versus control group, then the maximum predicted value is considered as final required sample size to assess the efficacy of the interaction effect and the main effects. A similar study ([19](#_ENREF_19)) is used to determine the sample size by T test to compare the means of QOL. The probability of type 1 error is 5% and the probability for type 2 error is 20%, so the calculated sample size is 21 persons per each group. The G power software version 3-1-7 is used to calculate sample size. The probability of dropout is considered 15%, so the predicted number increases to 30 for each group and we will require 120 patients with IBS. This number of patients is sufficient to find the interaction effect as 2 times of main effects, although we will need more sample size if we desire to find much smaller scale of differences.

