**Discussion**

Up to our knowledge, it will be the first factorial RCT of the impact of soy isoflavones and vitamin D on symptoms severity, QOL, total score, inflammatory markers and fecal serine protease activity in IBS. This study will be investigated to determine the efficacy of two interventions or their any probable synergistic effect on IBS.

IBS-SSS, IBS-QOL and total score will be recorded by face to face interview and similar training sessions will be held for all research team to reduce the information and selection bias and inter-individual variability among the interviewers.

The step by step manual for laboratory analysis will be provided to prevent any random error in long duration of investigations. Furthermore, all analyses will be done at research lab of DDRI to control any systematic error of lab systems and technicians.

The strength points of this study can be the following items: Vitamin D deficiency is prevalent in our country especially in Tehran because of the latitude of this city and the impact of air pollution, Moreover there is enough evidence on the deficiency of vitamin D especially in women with IBS, so we select the women with IBS that reside in Tehran. Data management will be done at -1 week, week 0, week 6 and week 10 by manually checking of data accuracy and relevancy by one the members of research team. Furthermore, the statistician will clean all data after entrance of all data in statistical software and will report any unreal data to data collection members to check again.

The amount of TNF-α and NF- κβ is a critical marker of mild inflammation level in IBS and the effect of intervention can be critical for future RCTs. Fecal serine protease is an acceptable and feasible marker for intestinal permeability that is safe and with the minimum offensive consequence on the intestinal tissues compared to biopsy samples of intestine during colonoscopy ([20](#_ENREF_20)).

This study can contribute to specify the marginal means of soy isoflavones and vitamin D and any interaction effect of them on clinical and biological outcomes in IBS ([21](#_ENREF_21)). The potential possibility of large lost to follow up in most clinical trials on IBS makes this clinical research inexplicit to report any realistic findings while it can be assuring to evaluate the efficacy and safety of the interventions in IBS for future larger population based RCTs.

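### The enquiry four weeks after treatment covers only women still in the trial, and the visible text gives no active adverse event enquiry for a woman who leaves before week 6 without reporting one

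*Protocol*

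**What the plan says.** The protocol's Safety section is one sentence with two parts. The first covers the whole study: "Any unfavorable reported symptoms will be recorded in specific forms". The second concerns the point four weeks after treatment stops, when "all the remained will be asked about the compliance of intervention, personal attitude on this study and any adverse events will be reported", a duty the sentence extends into follow-up.

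Three other places bear on this:

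- The Abstract, under Methods/design: "The adverse events will be recorded during all sessions of this trial".
- Exclusion criteria, which include grounds that can only arise after entry: "no desire to complete the study; adverse effect of supplement; pregnancy during study".
- The timetable. Treatment lasts 6 weeks with follow-up at week 10 (Design). Outcomes are taken at weeks 0 and 6, and the total score also at week 10 (Primary outcome, Secondary outcomes). Data checks are set for weeks -1, 0, 6 and 10 (Discussion). The visible text names no session between weeks 0 and 6.

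Sample Size plans for loss: "The probability of dropout is considered 15%, so the predicted number increases to 30 for each group". The Discussion warns that loss to follow-up may be large and says of the trial that "it can be assuring to evaluate the efficacy and safety of the interventions in IBS for future larger population based RCTs".

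**The concern.** Women who leave a trial early are among those in whom intolerance is most plausible. Here the one enquiry that the Safety section schedules is addressed to those who have not left. The other two routes depend on the woman: she must volunteer the symptom or attend the session. Someone who stops in week 3, gives no reason and does not come back meets neither condition.

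At stake is the completeness of the adverse event record. If silent leaving were more common in one arm, the recorded events would lean towards women who tolerated the capsules. The protocol wants the trial to inform the safety side of larger trials, and an analysis plan cannot recover events that nobody asked about.

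**Working it through.** The point is mainly textual, and there is no plan figure to reproduce. The first step sets the rules against the women they reach.

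**Who is covered**

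- *Attends week 6 and week 10:* covered by recording at sessions and by the post-treatment enquiry.
- *Attends week 6, lost before week 10:* covered at week 6 by recording at sessions; not asked afterwards.
- *Stops capsules but attends week 6:* covered by recording at sessions.
- *Leaves before week 6 and reports a symptom:* covered by the form for reported symptoms.
- *Removed for an adverse effect of the supplement:* the event is known, because it is the ground for removal.
- *Leaves before week 6, attends nothing later, volunteers nothing:* no rule in the visible text reaches her.

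Only the last group has no adverse event enquiry after she starts treatment.

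**What the enquiry asks**

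The persons asked are the subject of the verb; compliance and attitude are its object. Adverse events come next with a verb of their own. They may be a third topic of the same interview, or a separate duty to report whatever becomes known. On the first reading, women who have left are not asked about harm. On the second, nobody is expressly asked about harm in this enquiry, and still no contact with leavers is described.

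**Scale**

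Inputs from Sample Size: 120 women, 30 per group, planned dropout 15%, and 21 per group before allowance for dropout.

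- Expected leavers at the planned rate: 0.15 × 120 = 18, or 18 / 4 = 4.5 per arm.
- Loss that the step from 21 to 30 would absorb: 1 − 21/30 = 0.30, and 0.30 × 120 = 36 women. So 18 is not a limit even on the protocol's own numbers.
- Women affected = leavers × (share who leave before week 6 and attend nothing later) × (share of those with an adverse effect) × (share of those who do not mention it). The protocol gives none of the three shares. With 18 leavers the product can lie anywhere from 0 to 18; with 36, from 0 to 36.
- Effect of one missed woman with all randomised women as denominator: 1/30 = 3.3 percentage points in her arm, and 1/60 = 1.7 points on one side of a main-effect comparison.

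No event rate is assumed, and no difference between arms can be calculated from the documents.

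**The case against.** The strongest reply is that this is mostly silence, and that little is left once the existing rules are counted. Reported symptoms are recorded without restriction to completers, events are recorded at every session, and removals for an adverse effect are known by definition. The adverse event clause may not be limited to those who remain. Nothing in the text says that a woman who stops her capsules misses week 6; Statistical Analysis applies intention to treat to the primary and secondary outcomes, which at least leaves her attendance open. Fig. 1 could show an interim session or how discontinuation is handled. Adverse events are not a listed outcome, and no between-arm test of them is planned.

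Most of this stands, and it confines the point to women who both leave and say nothing. It does not remove the point. The Safety section chooses whom to ask and chooses those who remain. Reading the adverse event clause separately creates no contact with leavers, and an interim session would still miss anyone who left before it. Intention to treat is stated for outcome data and does not say that leavers are asked about harm.

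A reader might infer more: that harms in early leavers go unrecorded altogether, or that the adverse event comparison is biased. The documents support neither. The first ignores the three existing routes. The second needs a difference between arms in silent leaving, for which there is no evidence either way.

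**Conclusion.** The point holds in a limited form. The scheduled post-treatment enquiry is restricted to women still in the trial, its coverage of adverse events is unclear, and the visible text provides no active adverse event enquiry for a woman who leaves before week 6, attends no later session and volunteers nothing.

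The number affected is unknown and could be zero. The figure of 18 describes all leavers expected at the planned 15%. It might be read as a ceiling, or as the number of missed events, and it is neither. The conclusion assumes that Fig. 1 adds no contact at the time of stopping.

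This is a minor and cheap improvement to safety ascertainment. It is worth making because the information is hard to recover later and the protocol says it wants safety data. It casts no doubt on the primary or secondary outcomes.

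**What to change.** Amend the Safety section in two places.

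1. Replace the reference to those who remain with *all randomised women, including those who stopped early, unless they refuse further contact*. State that the enquiry includes adverse events and takes place four weeks after each woman's own last dose. For completers this is the existing week 10 follow-up.
2. Add: *any woman who stops early is asked at that time about adverse events and her reason for stopping, and the answers are recorded on the same form.*

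Sessions, doses, sample size and the exclusion criteria stay as they are.

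Cost: a short amendment and some calls. Assuming 5 to 10 minutes per contact and two contacts per early stopper, 18 women need 18 × 2 × 5 = 180 minutes to 18 × 2 × 10 = 360 minutes, that is 3 to 6 staff hours. With 36 women it would be 6 to 12 hours. Slightly more adverse events will be recorded. Some leavers will refuse contact, so the change narrows the gap without closing it.

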**Discussion**

Up to our knowledge, it will be the first factorial RCT of the impact of soy isoflavones and vitamin D on symptoms severity, QOL, total score, inflammatory markers and fecal serine protease activity in IBS. This study will be investigated to determine the efficacy of two interventions or their any probable synergistic effect on IBS.

IBS-SSS, IBS-QOL and total score will be recorded by face to face interview and similar training sessions will be held for all research team to reduce the information and selection bias and inter-individual variability among the interviewers.

The step by step manual for laboratory analysis will be provided to prevent any random error in long duration of investigations. Furthermore, all analyses will be done at research lab of DDRI to control any systematic error of lab systems and technicians.

The strength points of this study can be the following items: Vitamin D deficiency is prevalent in our country especially in Tehran because of the latitude of this city and the impact of air pollution, Moreover there is enough evidence on the deficiency of vitamin D especially in women with IBS, so we select the women with IBS that reside in Tehran. Data management will be done at -1 week, week 0, week 6 and week 10 by manually checking of data accuracy and relevancy by one the members of research team. Furthermore, the statistician will clean all data after entrance of all data in statistical software and will report any unreal data to data collection members to check again.

The amount of TNF-α and NF- κβ is a critical marker of mild inflammation level in IBS and the effect of intervention can be critical for future RCTs. Fecal serine protease is an acceptable and feasible marker for intestinal permeability that is safe and with the minimum offensive consequence on the intestinal tissues compared to biopsy samples of intestine during colonoscopy ([20](#_ENREF_20)).

This study can contribute to specify the marginal means of soy isoflavones and vitamin D and any interaction effect of them on clinical and biological outcomes in IBS ([21](#_ENREF_21)). The potential possibility of large lost to follow up in most clinical trials on IBS makes this clinical research inexplicit to report any realistic findings while it can be assuring to evaluate the efficacy and safety of the interventions in IBS for future larger population based RCTs.

**List of abbreviations:**

IBS: irritable bowel syndrome, SSS: Severity Scoring System, QOl: quality of life, RCT: randomized clinical trial, TNF-α: Tumor Necrosis Factor- alpha, NF- κβ: Nuclear Factor- Kappa Beta, ELISA: enzyme- linked immunosorbant assay, PBMC: Peripheral blood mononuclear cells, DDRI: Digestive Diseases Research Institute, TUMS: Tehran University of Medical Sciences, SBMU: Shahid Beheshti University of Medical Sciences, EDTA: ethylenediaminetetraacetic acid

**Competing interests:** There is no competing interest.

**Funding:** Shahid Beheshti University of Medical Sciences, Tehran, Iran.

